### Study procedures

#### Site setup

Recruitment will take place sequentially in each CDC area in order to ensure that the limited number of training devices are issued in the most efficient way. In preparation for recruitment, the research team will visit each site to familiarise physiotherapists with the eligibility criteria and trial procedures.

#### Recruitment

The physiotherapist will approach children and families on their caseload and give an information pack. Adverts for the study will be placed in clinic rooms, and on parent forums and social media. Potential participants who respond to the invitation will be screened for suitability using a telephone questionnaire to check diagnosis, age, GMFCS level and ability to play a game using a mouse or joystick. Eligible families will be approached for consent to be recruited to the qualitative study at baseline using a purposive sampling framework.

Potential participants who do not wish to take part in the study or withdraw from the study will be invited to undertake a short (less than 5 min) telephone interview to help understand any barriers and facilitators to participating in the trial, to aid in future recruitment. A separate information sheet will be available for these interviews.

### Data collection

#### Baseline visit

Written informed consent and assent will be recorded prior to the child and parent undertaking the first baseline measurement session. The following data will be collected at the first visit:

GMFCS level.Date of birth.Medical and surgical history.Height, weight, pelvic depth.Frequency and location of usual physiotherapy.Other sports and social activities.

### Outcome measures

The following assessments will be carried out at weeks 0 and 10, and those indicated with * at 20 weeks follow-up. The physical assessments will take 70 min, followed by goal setting. Qualitative semistructured interviews will take place after completion of the 10-week training.

#### Primary outcomes

*Medio-lateral motion of the centre of mass estimate.^10 11^*Paediatric Balance Scale.^12^

#### Secondary outcomes

*Walking kinematics*.*Muscle strength of quadriceps, hamstrings, and gastrocnemius and hip abductors using a hand held dynamometer (three measurements).*Passive range of movement and modified Tardieu scale^13^ of quadriceps, hamstrings, gastrocnemius and hip adductors using goniometer (three measurements).Canadian Occupational Performance Measure.^14^Child Health Utility instrument -CHU-9D—Paediatric Quality of Life measure.^15^

#### Blinding

This will be a single-blinded RCT. The assessor will be blinded to allocation while carrying out the assessments at baseline and week 10. It will not be possible to for the assessor to remain blinded to group allocation for the 12 participants taking part in qualitative interviews occurring at week 11. However, the assessor will remain blinded to group allocation at week 20 for the remaining participants who are not undertaking the interviews.

#### Randomisation

Participants will be randomly allocated at a ratio of 1:1 and will be minimised by age (above or below 9 years) and by GMFCS level (level I and II vs level III). This is because acquisition of gross motor ability peaks by age 9, and children above that age plateau or may decline in motor skills.^16^ The minimisation sequence and randomised allocations will be computer-generated in conjunction with an independent statistician. The blinded assessor will enter the details required for randomisation into the study website, book the participant’s first appointment with the treating therapist.

An email will be generated by the study website to inform the local treating physiotherapist of the participant’s allocated group. The treating physiotherapist will reveal group allocation to the participant at the first session. An unblinded researcher will arrange for the interactive trainer to be transported to the site where the child usually does their physiotherapy for example, school, CDC, home.

#### Qualitative assessment

This qualitative study uses novel ways of data collection with the children including semistructured e-diaries using electronic tablet devices and photo-elicitation interviews. Semistructured interviews will be undertaken with parents/carers and physiotherapists. Triangulation of the e-diaries and interviews will be used to provide credibility, ensuring that the understanding of the full scope of the experiences related to participating in the trial is as complete as possible from the perspectives of the children, parents and physiotherapists. Twelve parent–child dyads will be recruited (30% of the total sample of the feasibility study). Four physiotherapists, who have delivered the intervention and control treatments in different settings, will be interviewed. Sampling of up to eight parents who declined or withdrew their child from the study will be undertaken.

### Statistical analysis plan

A statistical analysis plan (SAP) will be drafted prior to the final database lock; the SAP will be agreed with the trial steering committee (TSC) in the absence of a data monitoring committee. A CONSORT diagram will be used to present descriptive data on screening, enrolment, intervention allocation, follow-up and assessment.

Completion rates of the intervention and outcomes collected at each time point will be reported with confidence intervals. All analyses and data summaries will be conducted on the intention-to-treat population, defined as all participants randomised regardless of non-compliance with the protocol or withdrawal from the study. Participants will be analysed according to the intervention they received.

The baseline characteristics of those lost to follow-up will be compared with those who complete the trial in order to identify any potential bias.

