## Objectives

The objectives of the study are to:

Determine the feasibility of a definitive trial.Determine the acceptability of the intervention.Explore the views of a subgroup of study participants.

The trial objectives will be measured by the outcomes set out in table 1.

**Table 1 T1:** Objectives of the feasibility study

Objective	Outcome
**Focus**	**Methods**
Feasibility of definitive trial	
Acceptability of the trial and intervention	Interviews of staff, parents and children
Can we recruit and retain participants?	No of participants eligible No recruited and randomised, date of recruitment recorded on study database Recruitment source No of withdrawals. No of participants lost to follow-up.
Effectiveness and acceptability of randomisation	Comparison of participant characteristics: severity, distribution of motor impairment, associated impairments at baseline Interviews
Effectiveness of concealment of allocation up to week 10	No of times chief investigator correctly guessed treatment allocation
Concurrence with other surgical and medical interventions	No of operations or procedures that target balance and walking during the intervention and follow-up period.
Change in clinical outcome measures	Change in assessment scores of outcome measures
Assess appropriateness of outcome measures	No and percentage of outcome measures completed at each time point Interviews
Feasibility of Intervention	
Adherence to treatment	Diary data frequency and duration of training
Acceptability of treatment intervention	Incidence of breakdown of equipment No of times participants were unable to access equipment Participant view on acceptability of interventions by interview
Cost of intervention and support needed to use it	Local physiotherapist record of staff time and grade used to support intervention. Travel costs of staff and families. No and cost of repairs
Safety of intervention	No and type of SAE and AE
Acceptability of participation	
Acceptability of participation	Themes identified from interviews/photos

AE, adverse event; SAE, serious adverse event.

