#### Proposed primary and secondary outcome analysis

The planned primary and secondary outcome measures will be reported at each time point using descriptive statistics. As this is a feasibility trial, it is not appropriate to perform a hypothesis test between-group treatment effects.^17^ Instead, the difference between allocated groups of the follow-up minus baseline score will be estimated with confidence intervals.

A sample size estimate for a definitive trial will be undertaken for the proposed primary outcome. Estimation of the SD, correlation between baseline and follow-up measures and a clinically meaningful difference will be used in the power calculation.

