### Sample size

As this study is a feasibility trial, it is not appropriate to use a sample size calculation based on considerations of power for detecting between group differences.^17^ The feasibility aims are to provide robust estimates of recruitment rate and follow-up as well as estimates of the variability of the outcome measures, which will in turn inform sample size calculations for a full RCT.

A sample size of 40 participants will allow the overall recruitment rate to be estimated. It is anticipated that follow-up of a minimum of 12 participants in each of the intervention and usual care groups would provide sufficient data to inform indicative sample size calculations for the definitive main trial. An estimated recruitment rate of three to four children per month over a 12-month period has been calculated based on population and previous experience.

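### The intention-to-treat paragraph ends with an as-treated grouping rule, which conflicts with the allocated-group comparison in the next section

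*Protocol article*

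**What the plan says.** The Statistical analysis plan section of the protocol article applies one population to everything: "All analyses and data summaries will be conducted on the intention-to-treat population, defined as all participants randomised regardless of non-compliance with the protocol or withdrawal". The next sentence states how participants are grouped: "Participants will be analysed according to the intervention they received".

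The next section, Proposed primary and secondary outcome analysis, states the one between-group comparison in different terms: "the difference between allocated groups of the follow-up minus baseline score will be estimated with confidence intervals". The same section plans estimation only, saying that "it is not appropriate to perform a hypothesis test between-group treatment effects".

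Nothing in the article confines the sentence about the intervention received to a safety, sensitivity or supplementary analysis. No separate as-treated or per-protocol set is defined.

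**The concern.** A child who is randomised to the device but has only usual care belongs to the device group under the outcome-analysis section and to usual care under the sentence in the analysis-plan section. Only one of these keeps the groups that randomisation and minimisation on age and GMFCS level created. Children who do not take up the device may differ from those who do, so grouping by receipt can produce a difference between arms when the device has no effect.

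The sentence also works against what a feasibility trial is meant to learn. Failure to deliver the allocated device is one of the things being measured: Table 1 under Objectives plans to count "No of times participants were unable to access equipment" and equipment breakdowns. The Intervention section gives four devices, and the Discussion expects that moving them around the community may be hard. A child the device never reached would leave the device arm's denominator, and intervention completion in that arm would look better than it was.

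This is not a detail left for the SAP, which is not among the documents at hand. The article states a rule, and the rule is wrong as written. The article requires the SAP to be drafted only before final database lock, so the conflict could remain open until departures from allocation are known.

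**Working it through.** The plan gives no figure to reproduce, so the check is a comparison of the text followed by an illustration.

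**Side by side**

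| Place in the protocol article | What it fixes | Rule |
|---|---|---|
| Statistical analysis plan, population sentence | Who is included | Everyone randomised, whatever their compliance |
| Statistical analysis plan, next sentence | How they are grouped | By intervention received |
| Proposed primary and secondary outcome analysis | How the difference is formed | By allocated group |

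The second and third rows agree only if every child receives the allocated intervention. The first and second rows also clash for a child who withdraws before the first session. The population sentence keeps that child in, but the received rule offers no arm to put the child in.

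**Inputs from the article.** Total 40 ("A sample size of 40 participants will allow the overall recruitment rate to be estimated") and "Participants will be randomly allocated at a ratio of 1:1", so about 40/2 = 20 per arm.

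**Assumed, because the article gives no value.** The number *k* of device-arm children who have only usual care, with no departures in the other direction.

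**Group sizes.** Allocated groups stay at 20/20. As-received groups are (20 − k)/(20 + k):

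- k = 0: 20/20
- k = 2: 18/22
- k = 3: 17/23
- k = 4: 16/24

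**Bias with no true effect.** Take k = 3, both allocated arms with mean 0, and the three children 0.5 SD below that mean (assumed), where SD is that of the change score.

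- Remaining device children: (3 × 0.5)/17 = 1.5/17 = +0.088 SD
- As-received usual care: −1.5/23 = −0.065 SD
- Spurious difference: 0.088 + 0.065 = 0.153 SD

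If the 0.5 SD deficit is instead measured against the other 17 device children, their mean is 1.5/20 = +0.075 and the three are at −0.425. The usual-care mean is then −1.275/23 = −0.055, and the difference is about 0.13 SD.

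**Set against precision.** The standard error of a difference at 20 per arm is √(1/20 + 1/20) = 0.316 SD, so the 95% half-width is about 2.02 × 0.316 = 0.64 SD. The illustrated bias is 0.153/0.64 = 0.24 of that half-width.

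**Intervention completion in the device arm (k = 3, all others complete).** As allocated: 17/20 = 85%. On an as-received denominator: 17/17 = 100%.

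**SD for planning.** Regrouping moves about 0.153²/4 = 0.006 of the variance from within to between groups. The within-group variance falls by about 0.6% and the SD by about 0.3%.

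**Pooled rates.** Recruitment, retention and outcome completion over all 40 children have the same numerators and denominators under either grouping.

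**The case against.** The strongest defence is that the population statement says only who is included, "defined as all participants randomised regardless of non-compliance with the protocol or withdrawal from the study", so grouping by receipt does not literally contradict it. This does not remove the conflict. Keeping non-compliers in and then sorting them by compliance defeats the purpose of intention-to-treat, and the outcome-analysis section names allocated groups in any case.

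A better objection is that the only between-group estimate set out in detail is already by allocation. The stray sentence then reads most naturally as a slip for the intervention participants were allocated. That is probably right, and it limits the damage: there is one specified comparison and one sentence that contradicts it, not two worked-out analyses. The sentence is nevertheless unqualified and follows directly on a statement covering all analyses and summaries, so it can still be applied.

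Three further points stand in part.

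- Non-uptake should be visible elsewhere, through the CONSORT diagram, diary adherence and the count of access failures. The 17/17 figure arises only if as-received denominators alone are reported.
- Recruitment runs area by area so that the few devices are used efficiently, and waiting for a device is not the same as switching treatment. Departures from allocation are foreseeable here, but their frequency is unknown.
- The 0.15 SD rests on assumed inputs, is small beside the confidence interval, and feeds no planned test.

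**Conclusion.** The contradiction is real. As written, the sentence directs an as-treated analysis that conflicts with the allocated-group comparison. If it were followed, the between-group difference and its confidence interval, by-arm outcome summaries and by-arm intervention completion would lose their basis in the randomised groups. Its size depends wholly on how many children do not receive what they were allocated: nil if none, and about 0.13 to 0.15 SD under the assumption of 3 in 20 with a 0.5 SD deficit.

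A reader might infer two larger consequences that the article does not support.

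- *That a biased treatment difference would be carried into the definitive trial.* The power calculation is to use the SD, the correlation between baseline and follow-up, and a clinically meaningful difference. The observed group difference is not among these, and the SD hardly moves.
- *That the progression decision would be distorted or device-arm retention inflated.* The Progression criteria section sets about 70% for recruitment and retention and 90% for outcome completion, with no thresholds by arm. A child who has usual care and gives outcomes is retained under either grouping.

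The consequence is moderate: an error to correct before analysis, but not one that undermines the trial's feasibility conclusions.

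**What to change.** Replace the sentence, in the protocol and in the SAP, with: *Participants will be analysed in the group to which they were randomised, regardless of the intervention received.* Label any summary by intervention received as supplementary. Report for each arm the number who did not receive their allocated intervention, as a feasibility result.

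The cost is one sentence and one reported count per arm. It needs no extra data from families and no change to the sample size. It should be settled before anyone has seen which children departed from their allocation.

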#### Proposed primary and secondary outcome analysis

The planned primary and secondary outcome measures will be reported at each time point using descriptive statistics. As this is a feasibility trial, it is not appropriate to perform a hypothesis test between-group treatment effects.^17^ Instead, the difference between allocated groups of the follow-up minus baseline score will be estimated with confidence intervals.

A sample size estimate for a definitive trial will be undertaken for the proposed primary outcome. Estimation of the SD, correlation between baseline and follow-up measures and a clinically meaningful difference will be used in the power calculation.

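### The between-group difference is planned as a raw change-score contrast; a baseline-adjusted estimate would usually be modestly more precise

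*Protocol article*

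**What the plan says.** The Protocol article, under Proposed primary and secondary outcome analysis, plans descriptive statistics at each time point and holds that "it is not appropriate to perform a hypothesis test between-group treatment effects". In place of a test, "the difference between allocated groups of the follow-up minus baseline score will be estimated with confidence intervals". No covariate or model is named for this contrast.

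Under Randomisation, 1:1 allocation "will be minimised by age (above or below 9 years) and by GMFCS level (level I and II vs level III". The age cut is justified there by the course of gross motor development, which is said to level off or fall after that age.

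The next paragraph of the analysis section turns to the definitive trial: "Estimation of the SD, correlation between baseline and follow-up measures and a clinically meaningful difference will be used in the power calculation".

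On size, the article says "A sample size of 40 participants will allow the overall recruitment rate to be estimated", and looks for "follow-up of a minimum of 12 participants in each of the intervention and usual care groups" as enough to inform the later calculation. A separate SAP is to be drafted before database lock; it is not at hand.

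**The concern.** The between-group interval is the only comparative result on clinical outcomes that the trial will publish. Subtracting baseline assumes that each unit of baseline difference carries over in full to follow-up. When the true slope is below 1, subtraction over-corrects. The interval is then wider than it need be, and the realised estimate moves with whatever baseline imbalance chance has produced.

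Age group and GMFCS level were judged important enough to balance by design, yet the stated contrast does not use them. On the article's own rationale, age may predict change itself, and subtracting baseline would not remove that. Both factors and the baseline scores are collected anyway, so the precision is available without extra data.

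**Working it through.** **Inputs from the article.** 40 participants at 1:1 give 20 per arm; the minimum followed up is 12 per arm. The article states no SD, correlation or interval width for any outcome, and the sample size is not power-based, so there is no planned figure to reproduce.

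**Assumptions, not from the article.** SDs are equal at baseline and follow-up (set to 1), the relation is linear, and rho is 0.5, 0.7 or 0.9.

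**Step 1: residual spread.**
- Change score: SD = sqrt(2(1 − rho)), which gives 1.000, 0.775 and 0.447.
- Baseline-adjusted: SD = sqrt(1 − rho²), which gives 0.866, 0.714 and 0.436.
- Large-sample variance ratio, adjusted to change: (1 − rho²) / (2(1 − rho)) = (1 + rho)/2, which gives 0.75, 0.85 and 0.95. It is below 1 whenever rho < 1.

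**Step 2: 95% interval half-width in a small trial.** With n per arm and N = 2n:
- Change: t(0.975, N − 2) × sqrt(2(1 − rho)) × sqrt(2/n).
- Adjusted for baseline: t(0.975, N − 3) × sqrt(1 − rho²) × sqrt(2/n) × sqrt(1 + 1/(N − 4)). The last factor is the price of estimating the slope.

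| n per arm | rho | Change | Adjusted | Ratio |
|---|---|---|---|---|
| 20 | 0.5 | 0.640 | 0.563 | 0.879 |
| 20 | 0.7 | 0.496 | 0.464 | 0.936 |
| 20 | 0.9 | 0.286 | 0.283 | 0.989 |
| 12 | 0.5 | 0.847 | 0.753 | 0.890 |
| 12 | 0.7 | 0.656 | 0.621 | 0.947 |
| 12 | 0.9 | 0.379 | 0.379 | 1.002 |

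With 20 per arm the intervals are therefore about 12%, 6% and 1% narrower.

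**Step 3: cost of the two minimisation factors if they explain nothing further.** Degrees of freedom fall to N − 5. With 20 per arm the ratios become 0.880, 0.937 and 0.991. With 12 per arm at rho 0.9 the ratio is 1.008, a loss of under 1%. If the factors do predict outcome there is a gain, which cannot be sized from the article.

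**Step 4: simulation, 10,000 runs per case, normal data, no true effect.** Variance ratios were 0.77, 0.88 and 0.98 with 20 per arm, and 0.78, 0.90 and 1.00 with 12 per arm. The mean of each estimator was within 0.003 SD of zero in every case, so both are unbiased over randomisation.

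**Step 5: dependence on the realised imbalance.** Given a baseline difference D between groups, the change-score contrast shifts by (1 − rho) × D, in the direction opposite to D. As an illustration, one standard error of D under simple randomisation with 20 per arm is sqrt(2/20) = 0.316 SD. The shift is then 0.5 × 0.316 = 0.158 SD at rho 0.5, 0.3 × 0.316 = 0.095 SD at rho 0.7 and 0.1 × 0.316 = 0.032 SD at rho 0.9. Minimisation would make D smaller to the extent that age and GMFCS level predict baseline scores.

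**Step 6: what the definitive trial needs.** The planned SD and "correlation between baseline and follow-up measures" already give the baseline-adjusted residual SD as SD × sqrt(1 − rho²), for example 0.714 SD at rho 0.7.

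**The case against.** The strongest reply has four parts.

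- **The wording does not exclude adjustment.** Regressing change on group and baseline gives the same group coefficient and residual SD as regressing follow-up on group and baseline, and the unseen SAP may name covariates. The algebra is right, and missing covariates alone would be no finding. But the article does state its estimator, and the plain reading of that sentence is a simple difference in change.
- **The trial already provides for the next one.** A reader might infer that the plan ignores the baseline correlation and leaves the definitive trial without the SD it needs. The article does not support this: the correlation is unused only in the between-group contrast, and the planned SD and correlation yield the residual SD (step 6). A fitted model adds the residual SD after age and GMFCS level, and a check on the equal-SD and linearity assumptions.
- **There is no bias.** A reader might infer that the contrast is biased, or its interval invalid because the minimisation factors are left out. Neither follows. The contrast is unbiased over randomisation, and omitting balanced prognostic factors tends to make the interval too wide. The conditional shift in step 5 and the wider interval are two views of one weakness and should not be counted twice.
- **Nothing is decided on this interval.** No test is planned, progression rests on recruitment, retention and outcome completion, and the objectives table lists change in scores as an outcome. All of this stands and limits the weight of the point. It does not remove the gain, because the interval is the stated between-group result.

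**Conclusion.** The point holds as a modest matter of efficiency. The stated contrast is unbiased but generally less precise than a baseline-adjusted difference, and it shifts with chance baseline imbalance. With 20 per arm, adjustment would narrow the 95% interval by about 12% at rho 0.5 and 6% at rho 0.7. At rho 0.9 the gain is about 1%, and with 12 per arm it is nil.

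These sizes rest on equal SDs, a linear relation and assumed values of rho, none of which the article gives. Feasibility conclusions and the progression criteria are unaffected.

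**What to change.** In the SAP, and in the protocol wording if it is amended, replace the raw contrast with an adjusted mean difference and 95% CI. Use a linear model of follow-up score on allocated group, baseline score, age group (9-year cut) and GMFCS level (I–II v III). Fit it at week 10, and at week 20 for the outcomes measured then. No hypothesis test is needed. Keep raw change by group as a descriptive summary, which still serves the objective on change in scores. Report the model's residual SD alongside the SD and baseline/follow-up correlation already planned for the definitive sample size.

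The cost is wording and three degrees of freedom; all variables are already collected. If rho is very high and the factors are not prognostic, the precision loss is negligible (under 1% of interval width with 12 per arm at rho 0.9).
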